#### EMA data analysis

Consistent with previous work using a highly individualized approach [102] to treatment and assessment, self-regulatory responses from EMA periods will also be used to conduct moderation and mediation analyses. Moderation analyses will test the extent to which daily ratings of readiness-to-change, alcohol coping self-efficacy, and alcohol-related planning, moderate the effect of the INTV intervention on alcohol use. Mediational analyses will test the extent to which the intervention reduces both alcohol use and chronic pain through changes in self-regulatory processes when exposed to relevant contexts. Analyses will use aggregated scores from events in which the participant indicates that they were exposed to relevant contexts, including moderate or greater pain, or the opportunity to use alcohol [102]. As with the questionnaire data, we will use structural equation modeling (SEM) to test the hypothesis that increases in context-specific self-efficacy and planning will mediate the relationship between condition (INTV vs. CTL) and 6-month outcomes. Bias-corrected bootstrap confidence interval estimates will be used to test the mediation hypotheses [103]. As described, power of > 80% is estimated when the standardized effect of path a and path b represents a small-to-medium effect. Covariates in the EMA analyses will include the number of event monitoring events completed, as well as the number of relevant pain or drinking opportunity events identified.

EMA data will also contribute to several exploratory analyses which address event level questions, including how the intervention influences associations between cues (e.g., mood) and pain and alcohol use outcomes. It is hypothesized that, when day is included as a covariate to control for potential systematic changes over time, higher negative mood earlier in the day will be associated with higher chronic pain or unhealthy drinking later in the day. Within-subject associations between mood and chronic pain or unhealthy drinking may vary by treatment group, and it is hypothesized that those randomized to INTV will demonstrate attenuated associations relative to the CTL group.

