### Overall design

Participants will be PLWH who engage in unhealthy drinking and experience moderate or greater chronic pain recruited nationally via online advertisement. Those who are eligible based on an initial set of online prescreening questions will be contacted by study staff for a more comprehensive phone screening. Those who remain eligible based on the more extensive screening will be scheduled for baseline assessment during which they will provide informed consent, confirm HIV diagnosis, and complete baseline questionnaires administered in an interview format. Staff will also orient participants to the EMA procedures whereby they will complete 5 surveys per day for the following 15 days. After EMA data collection, participants will undergo 1:1 randomization into either the intervention group (INTV) or the control (CTL) group. The INTV condition is a 7-session program designed for weekly delivery through videoconferencing by a health coach. Those in the CTL group meet virtually with the health coach for a single session and be provided with information and resources about alcohol and pain. At three-month outcome assessment, staff will administer questionnaires via interview, prior to another 15 days of EMA data collection. The final study assessment occurs six months after randomization and will include a staff-administered interview and a self-collected blood draw to measure phosphatidylethanol (PEth), a biological marker of alcohol use (see [29]). Participants complete self-collected blood draws at home and with guidance through videoconferencing (Fig. 1).

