#### Secondary aims

Secondary aims seek to identify potential moderators and mediators of INTV, using data from assessment interviews and EMA. It is hypothesized that the influence of the intervention will be moderated by baseline readiness-to-change (for alcohol) and baseline GSAB questionnaire ratings of self-efficacy and planning (for both alcohol and pain outcomes). Secondary aims pertaining to alcohol use will be addressed by using baseline interview measures and parallel analyses will be conducted using baseline daily EMA ratings of readiness-to-change, alcohol coping self-efficacy, and alcohol-related planning. Mediational analyses will also be conducted using EMA at the 3-month outcome to test hypothesis that changes in self-regulatory processes mediate the effect of the INTV on alcohol use and chronic pain.

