### Assessments

#### Assessment procedures

Assessments will include interview-administered instruments at baseline, 3 months post-randomization, and 6 months post-randomization. In addition, there will be two 15-day EMA data collection periods (one at baseline and one at 3-months), a treatment satisfaction measure, and a blood draw to test a biological marker of alcohol use, phosphatidylethanol (PEth; [29]) self-administered 6 months-post randomization.

Participants will complete all assessment interviews (baseline, 3-month follow-up, and 6-month follow-up) virtually through a videoconferencing platform or by phone. Interviews will take approximately 90 to 120 min and are each associated with $50 compensation for time and effort.

In addition to research interviews, participants will complete two phases of EMA data collection over 15-day periods. The first 15-day EMA period begins following the baseline interview while the second 15-day EMA period takes place following the 3-month assessment interview. Participants will learn about EMA procedures following the baseline interview, including how to use the EMA iOS or Android mobile application (MetricWire; [36]. Each day during the EMA periods, MetricWire will prompt participants to complete a morning survey and four additional surveys which arrive randomly throughout the day.

Upon completing the 15 days of EMA surveys at the 3-month time point, participants will be notified to complete one final survey on intervention satisfaction and acceptability for which they will be compensated $5. Across all study activities, participants will be able to earn up to $480 over the 6 months. Payments are made via electronic gift certificates.

Finally, at the 6-month outcome assessment interview, participants will be able to earn an additional $25 for completing and sending a self-administered blood sample to the collaborating laboratory [29].

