### Statistical design and analysis

#### Sample size determination

A sample size of 250 (*n* = 125 to each condition) will be randomized. With a conservative estimate of a 20% attrition rate by 6-month follow-up, this sample size gives power (80%) to detect medium effects (Cohen’s d = 0.40) at the 2-tailed significance level (0.05) for INTV versus CTL at 6-month follow-up on both pain and alcohol outcomes. The anticipated effect size is based on the following: (1) meta-analyses of CBT interventions compared to assessment and minimal interventions suggesting medium post-intervention effects on alcohol and pain; [98–100] and (2) results of our pilot study which showed medium-to-large pre-to-post changes (Cohen’s d from 0.79 to 1.0) within participants receiving INTV [95, 96]. Moreover, the availability of repeated measurements (to include a baseline covariate) increases statistical power to detect intervention effects for the analysis.

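### The EMA mediators are measured after the month-3 drinking and pain outcomes, and those outcomes are not among the covariates named for the 6-month mediation model, so an indirect effect can appear where the mediator has none

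*Protocol article*

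**What the plan says.** *Overall design* describes the intervention: "The INTV condition is a 7-session program designed for weekly delivery through videoconferencing by a health coach". Delivered as designed, it ends well before month 3. At month 3 staff give the interview first. Table 1 schedules both the TLFB-30 and the PEG in it, and the TLFB-30 looks back 30 days. *Assessment procedures* then states that "the second 15-day EMA period takes place following the 3-month assessment interview".

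The mediators are taken from that second EMA period. *Secondary aims* says: "Mediational analyses will also be conducted using EMA at the 3-month outcome to test hypothesis that changes in self-regulatory processes mediate" the INTV effect on drinking and pain. *EMA data analysis* specifies structural equation modelling with bias-corrected bootstrap intervals for the hypothesis that "increases in context-specific self-efficacy and planning will mediate the relationship between condition (INTV vs. CTL) and 6-month outcomes".

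Covariates are named in two places. *EMA data analysis* lists two counts: EMA reports completed, and relevant pain or drinking-opportunity events. *Primary and secondary analyses* lists age, sex at birth and baseline values. Neither section names the month-3 drinking or PEG value, and neither describes a model in the reverse order.

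**The concern.** Randomisation protects the path from condition to mediator and the path from condition to outcome. It does not protect the path from mediator to outcome. Here the month-3 outcome comes before the mediator, may well influence it (someone already drinking less or hurting less may feel more able to cope), and is likely to predict the month-6 outcome. Left out of the outcome equation, it confounds that path.

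The article expects medium post-intervention effects, so some change by month 3 is part of its own premise. Identifying mediational pathways is a stated secondary aim, and the hypothesis has a direction: self-regulation changes first, and drinking and pain follow. The model as described cannot tell that order from the opposite one.

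**Working it through.** **1. The plan's own figure.** *Sample size determination* gives "A sample size of 250", "a conservative estimate of a 20% attrition rate by 6-month follow-up", and "this sample size gives power (80%) to detect medium effects" (d = 0.40) at the "2-tailed significance level (0.05").
- Per arm: 2 × (1.960 + 0.842)² / 0.40² = 98.1, so 99. In total 198, and 198 / 0.80 = 247.5, so 248 against the stated 250.
- Power with 100 per arm: Φ(0.40 × √50 − 1.96) = Φ(0.868) = 80.7%.

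The figure reproduces. The check below uses its 200 completers.

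**2. Assumed model.** The article gives no path values, so everything here is an assumption. X is condition, Y0, Y3 and Y6 the outcome at baseline, month 3 and month 6, and M0 and M the mediator at baseline and in the month-3 EMA.
- Y3 = 0.5·Y0 − d·X + error (variance 1 − 0.5² = 0.75)
- M = 0.4·M0 − k·Y3 + error (SD 0.8, variance 0.64)
- Y6 = 0.6·Y3 + 0.1·Y0 + error (SD 0.75)

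M has no effect on Y6, so the true indirect effect through M is zero.

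**3. Bias by algebra.** Fit M on X, M0, Y0, and Y6 on M, X, M0, Y0, leaving Y3 out.
- a = k·d
- false b = −0.6 × k × 0.75 / (0.75k² + 0.64)
- total effect on Y6 = −0.6·d
- apparent mediated share = 0.75k² / (0.75k² + 0.64)

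For d = 0.4, k = 0.3: a = 0.12, b = −0.135 / 0.7075 = −0.191, a·b = −0.023. Against a total of −0.24 that is a share of 9.5%. For k = 0.2 the share is 0.03 / 0.67 = 4.5%; for k = 0.5 it is 0.1875 / 0.8275 = 22.7%.

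**4. Simulation.** 1,000 trials per row, n = 200, indirect effect tested by a 95% Monte Carlo interval. The proxy column adds a variable correlated about 0.5 with Y3, standing in for the event counts.

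| d | k | Mean false a·b | Significant, Y3 omitted | Significant, proxy added | Significant, Y3 added |
|---|---|---|---|---|---|
| 0.4 | 0.2 | −0.010 | 3.1% | 1.7% | 0.4% |
| 0.4 | 0.3 | −0.023 | 11.0% | 5.3% | 0.7% |
| 0.4 | 0.5 | −0.053 | 31.9% | 21.1% | 1.2% |
| 0.6 | 0.2 | −0.015 | 4.8% | 2.5% | 0.2% |
| 0.6 | 0.3 | −0.033 | 19.6% | 9.3% | 1.0% |
| 0.6 | 0.5 | −0.081 | 61.7% | 39.4% | 3.3% |
| 0.8 | 0.2 | −0.021 | 9.1% | 4.6% | 0.3% |
| 0.8 | 0.3 | −0.046 | 33.3% | 16.0% | 2.4% |
| 0.8 | 0.5 | −0.109 | 83.2% | 61.6% | 4.2% |

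Seven of the nine settings lie between about 5% and 62% when Y3 is omitted. With Y3 added, the mean indirect effect is about zero throughout. With d = 0 (no month-3 effect, k = 0.3) the rate is 3.4%. With n = 2,000, d = 0.4 and k = 0.3 it is 86% without Y3 and 2% with it, so this is bias and not noise.

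A second specification (d = 0.4, k from 0.3 to 0.5, Y3-to-Y6 slope from 0.4 to 0.7, both paths required to be significant, 4,000 trials per setting) gave false mediation in 5% to 35% of trials and an apparent share of 8% to 25%. Adding Y3 brought false mediation to 2% or less.

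**5. What adjustment does when mediation is real** (n = 200, no reverse path).
- *Mediator acts only after month 3* (condition to M 0.4, M to Y6 0.2, true product 0.08): the estimate is −0.081 without Y3 and −0.082 with it; detection is 65% and 81%.
- *Mediator acts before month 3 and the gain persists* (condition to mediator 0.4 to 0.5, mediator to Y3 0.4 to 0.5, Y3 to Y6 0.6, mediator stability 0.8 to 0.9): the true indirect effect runs from 0.4 × 0.4 × 0.6 = 0.10 to 0.5 × 0.5 × 0.6 = 0.15 SD. Detection is 46% to 74% without Y3. With Y3 the estimate is about zero and detection is 4% to 6%.

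**The case against.** - **The covariate list is open.** The article says what the covariates will include, not that there are no others, and it writes out no equations. A reader might infer that the month-3 outcome was deliberately excluded; the text does not show that. What stands is narrower: the section goes as far as naming the method, the interval and specific covariates, and the one that matters for the direction of effect is not among them.
- **The event counts carry some of the information.** Someone hurting or drinking less will tend to report fewer relevant events. That is fair, and it lowers the error. At the assumed correlation of 0.5, about two thirds of the bias remains (0.0149 / 0.0232 = 64%; 0.0357 / 0.0532 = 67%).
- **The mediator precedes the 6-month outcome.** True, and the sequence is conventional. It does not deal with an outcome change that came before the mediator and persisted.
- **Adjustment can erase true mediation.** This is the strongest objection, and it stands. Sessions meant to raise self-efficacy may act before month 3, and step 5 shows that the adjusted model then almost always misses the effect. The adjusted model therefore answers a different question, and it cannot serve as the sole test of the mechanism.

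**Conclusion.** The point holds as a limit on what the planned mediation model can show. With no true mediator effect, the model falsely declared mediation in roughly 5% to 60% of simulated trials across most assumed settings (extremes 3% and 83%), with an apparent share of about 4% to 23% of the total effect in the tabulated settings. This requires both an INTV effect on the outcome by month 3 and a mediator that responds to it. Without the first, the error stays within the nominal 5%; where the response is weak, the bias is modest. The simulations used a Monte Carlo interval or joint significance in place of the planned bias-corrected bootstrap, whose rates may differ somewhat.

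A reader might infer that the planned model will report mediation regardless of the truth. The figures do not support that: in most of the settings, most trials showed no significant indirect effect. Nor does the point touch the primary efficacy comparison, which does not use the mediators.

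**What to change.** Keep the planned model and pre-specify one of these beside it:
- a second model that adds the month-3 value of the same outcome (TLFB-30 drinks per week, heavy drinking days, or PEG) to the outcome equation, with baseline outcome and baseline mediator; or
- a cross-lagged model, with the reverse order (condition to month-3 outcome to EMA mediator) as a sensitivity analysis.

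Report both results. Claim that self-regulation drove the 6-month change only when the adjusted path supports it. Otherwise state that the design cannot separate early mediation from reverse order, and do not read the loss of the adjusted path as evidence against the mechanism.

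The cost is a few lines in the analysis plan; Table 1 already schedules the data. The downside is some possible loss of power, and an adjusted estimate that excludes any mediation already realised by month 3.

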This paper describes a study protocol for a randomized controlled trial (RCT) that aims to test the efficacy of an integrated telehealth intervention for reducing unhealthy drinking and chronic pain among PLWH that may be implemented in a fully remote context. The secondary aims are to examine the moderators of the Motivational and Cognitive-Behavioral Management for Alcohol and Pain (INTV) effect and the mediational pathways of the INTV effect. Baseline interview-administered self-report and ecological momentary assessment (EMA) will be used to identify potential individual difference factors that moderate intervention efficacy. Post-intervention EMA, which provides the advantage of real-time assessment of self-regulatory processes and contextual influences on those processes, will be used to identify potential mediators of the intervention and explore mechanisms of behavior change [27, 28].

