#### Primary and secondary analyses

Descriptive statistics will be provided for the baseline characteristics of the full sample and by condition (i.e., INTV vs. CTL). Multiple linear regression analyses will be used to test whether those in the INTV group consume fewer drinks per week, engage in fewer episodes of heavy episodic drinking, and report lower PEG ratings than those in the CTL group at 6-month outcome. Covariates will include age, sex at birth, and corresponding baseline measures of alcohol use and pain. Secondary analyses will examine related outcomes (i.e. alcohol related consequences, pain intensity, pain severity) using a parallel approach. Exploratory analyses will examine INTV effects on outcomes including substance use frequency, depressive symptoms, anxiety symptoms, HIV symptom index scores, HIV risk-taking behaviors, mental functioning, and physical functioning at 6 months using multivariate regression models. For PEth analyses, we will use the lower limit of quantification as a cut-off of > 50 as a measure of unhealthy alcohol use and a cutoff of PEth > 8 ng/ml) as a marker of any alcohol use. Logistic multiple regression with the age and race/ethnicity will be used to examine intervention effects on 6-month PEth outcomes [101]. Secondary aims will be addressed, in part, by using baseline interview measures of readiness-to-change (for alcohol) and baseline GSAB questionnaire ratings of self-efficacy and planning (for both alcohol and pain outcomes). Planned covariates include those described under primary aims and will include baseline values of the questionnaire measure being evaluated. The Condition x Moderator term will be added to the full models to examine interaction effects, which will be followed with simple slopes analyses to determine the direction of effects.

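### The EMA mediation analysis does not fix whether the mediator is the 3-month score or a change, and does not name the baseline EMA score as a covariate; without it the indirect effect depends on the definition chosen

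*Protocol article*

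**What the plan says.** Five places in the protocol article bear on this.

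- **Introduction, last paragraph.** Post-intervention EMA "will be used to identify potential mediators of the intervention and explore mechanisms of behavior change". This points to a score from the second EMA period.
- **Secondary aims.** "Mediational analyses will also be conducted using EMA at the 3-month outcome to test hypothesis that changes in self-regulatory processes mediate" the intervention effect on alcohol use and pain. The 3-month period and the word for change stand in one sentence.
- **EMA data analysis.** The hypothesis is that "increases in context-specific self-efficacy and planning will mediate the relationship between condition (INTV vs. CTL) and 6-month outcomes". The scores are aggregated over entries made in relevant contexts, meaning pain of at least moderate level or an opportunity to drink. The method is a structural equation model with bias-corrected bootstrap intervals.
- **EMA data analysis, covariates.** "Covariates in the EMA analyses will include the number of event monitoring events completed"; the only other one named is a count of relevant pain or drinking-opportunity entries.
- **Primary and secondary analyses.** For the interview-based secondary aims, the planned covariates are those of the primary aim and "will include baseline values of the questionnaire measure being evaluated".

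Overall design and Assessment procedures place the first 15-day EMA period after the baseline interview and before randomisation, so a baseline EMA score will exist.

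**The concern.** Condition is randomised; the mediator is not. Participants who already have high self-efficacy or plan well before treatment will tend to do so at 3 months, and the same trait may influence drinking or pain at 6 months. The pre-randomisation EMA score is the measurement that can separate this from a mediator effect.

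If that score is left out, the choice between a 3-month score and a change score matters. The two give different mediator-to-outcome paths from the same data, and the protocol article leaves the choice open. One version could understate a real mechanism while the other overstates it. Mediation through self-regulation is a named secondary aim, so the choice should be settled before outcome data are seen.

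**Working it through.** **The plan's own figures.** Sample size determination starts from "A sample size of 250", 125 per arm. "With a conservative estimate of a 20% attrition rate by 6-month follow-up", this leaves 250 × 0.80 = 200, or 100 per arm. For d = 0.40, two-sided 0.05 and 80% power, the requirement is 99 per arm. Then 99/0.80 rounds up to 124 per arm, 248 in all, against 250 stated. Power with 100 per arm is 0.807 (normal) or 0.804 (t-test). The primary calculation reproduces.

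For mediation, the article claims more than 80% power for small-to-medium paths a and b, with no number attached. A joint-significance approximation at N = 200 gives 0.25, 0.65 and 0.92 for a = b = 0.14, 0.20 and 0.26. The claim is attainable but depends on an unstated value. No size of indirect effect is given, so what follows rests on assumptions.

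**Model.** X is condition, M0 the baseline and M3 the 3-month EMA score. Within arm, both scores have variance 1 and correlation rho. The outcome is Y = b·M3 + g·M0 + c'·X + error.

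**Path a.** Randomisation balances M0 in expectation, so the effect of X on M3 and on M3 − M0 is the same. Only path b is affected.

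**Path b without M0 in the model.**
- 3-month score: cov(Y, M3)/var(M3) = b + g·rho.
- Change score: cov(Y, M3 − M0)/var(M3 − M0) = [b(1 − rho) − g(1 − rho)]/[2(1 − rho)] = (b − g)/2.

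The bias is g·rho for the 3-month score and −(b + g)/2 for the change score. With b and rho not zero, these cannot both vanish: the first needs g = 0, the second g = −b.

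**Numbers.** Assumed: b = 0.30, rho from 0.3 to 0.8, g from −0.30 to +0.30.

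| rho | g | 3-month score (bias) | change score (bias) | ratio |
|---|---|---|---|---|
| 0.5 | −0.30 | 0.150 (−50%) | 0.300 (0%) | 0.5 |
| 0.5 | −0.15 | 0.225 (−25%) | 0.225 (−25%) | 1.0 |
| 0.5 | 0 | 0.300 (0%) | 0.150 (−50%) | 2.0 |
| 0.5 | +0.15 | 0.375 (+25%) | 0.075 (−75%) | 5.0 |
| 0.8 | −0.30 | 0.060 (−80%) | 0.300 (0%) | 0.2 |
| 0.8 | +0.15 | 0.420 (+40%) | 0.075 (−75%) | 5.6 |

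At g = b the change-score path is zero and the ratio is undefined. If b = 0 but g is not, the two paths tend to g·rho and −g/2: both non-zero and, for positive rho, of opposite sign.

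**With M0 in both equations.** Since M3 = (M3 − M0) + M0, the outcome can be written b·(M3 − M0) + (b + g)·M0 + c'·X + error. The coefficient is b under either definition, path a is unchanged, and the indirect effect is a·b both ways.

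**Simulation check.** Settings: a = 0.40, b = −0.30 (more self-efficacy, less drinking or pain), true indirect effect −0.12, rho = 0.5, g = 0, baseline outcome adjusted. The value 0.40 is borrowed from the sample size section, where it refers to the outcomes and not to a mediator.
- 1,000,000 subjects: 3-month −0.120, change −0.064, and −0.120 for both definitions once M0 is included.
- N = 200, 3,000 replicates: 3-month −0.118 (SD 0.049), change −0.063 (SD 0.034), both definitions with M0 −0.118 (SD 0.046).
- Month-3 variance 0.7 times baseline: −0.121 against −0.044 (ratio 2.7). At 1.5 times: −0.121 against −0.087 (ratio 1.4).

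**The case against.** The strongest reply is that nothing here is contradictory. The Introduction says which EMA period supplies the mediators. Change and increase are ordinary words for a mediation hypothesis, and no sentence mentions subtracting baseline. The Discussion credits EMA both before and after the intervention. A 3-month score adjusted for baseline fits every sentence. This stands: a reader might infer that the article specifies two incompatible mediators, and the text does not support that.

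Second, the covariate sentence is open-ended. It also leaves out age, sex at birth and the baseline outcome, which nobody would take as excluded. The EMA section says the model is used as with the questionnaire data, for which the baseline value is named. An article may also leave such detail to a full protocol or analysis plan that is not shown. This stands in part. The baseline EMA score cannot be said to be excluded. But the article gives the EMA analyses their own covariate sentence and goes into aggregation, model and bootstrap. The one covariate that would make the competing wordings equivalent is not named.

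Third, the size depends on assumed coefficients. This stands fully. A reader might infer that the definitions always differ two-fold, or that both always go wrong. Two-fold is the case g = 0 with equal variances. With g = 0 only the change score is biased, and with g = −b only the 3-month score.

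Fourth, a rule against difference scores would be a preference. That also stands: once baseline is in both equations, a difference score gives the same indirect effect.

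**Conclusion.** The point holds as an ambiguity with a material consequence. The mediator is not fixed, and the baseline EMA score is not named in the mediation model although it is collected. If the model were fitted without it, the estimated mediator path would be b + g·rho or (b − g)/2, depending on the definition. For non-zero b and rho at least one of these is biased, and for most values of g both are. The ratio between them ran from about 0.2 through 1.0 to above 5 under the assumed values. The documents give no correlation, variance or path coefficient from which to narrow that range.

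The result assumes a linear model and, for the closed forms, equal variances. Baseline adjustment returns b when the baseline score is the only omitted common cause; it does not remove confounding by other unmeasured factors.

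The matter is confined to a secondary aim. It would be wrong to infer that the efficacy tests or the 250 participants are affected. The change is still worth making, because it needs no new data.

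**What to change.** State one mediator definition and use it in the Introduction, Secondary aims and EMA data analysis: for example, the aggregated context-specific EMA score at 3 months. In EMA data analysis, name the baseline EMA score of the same measure as a covariate in both the mediator and the outcome equations, alongside the baseline outcome, age, sex at birth and the two event counts already listed. If the full protocol or analysis plan already does this, a clause in line with it is enough.

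The cost is wording only, since the baseline EMA is already scheduled. One small downside: a participant who reports no relevant context during the baseline EMA period has no context-specific baseline score. Full-information maximum likelihood or imputation of that covariate would be needed and should be named.

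### Read naturally, the EMA mediation models adjust for a 3-month count of pain or drinking-opportunity events that the intervention may change, so path a may not be a randomised contrast

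*Protocol article*

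**What the plan says.** Under Secondary aims, the protocol article states "Mediational analyses will also be conducted using EMA at the 3-month outcome". Overall design and Assessment procedures place that second 15-day EMA period after the 3-month interview. It therefore follows randomisation and the planned end of seven weekly sessions.

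Under EMA data analysis, the self-regulation scores are built from selected prompts: "Analyses will use aggregated scores from events in which the participant indicates that they were exposed to relevant contexts". The contexts named are pain of at least moderate level and a chance to drink. The section then gives one covariate list for all EMA analyses: the number of surveys completed, "as well as the number of relevant pain or drinking opportunity events identified".

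The text does not say which EMA period the count comes from. Nor does it say whether the count enters the mediator equation, the outcome equation or both.

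**The concern.** Path a, from arm to mediator, is the only link in a mediation model that randomisation protects. It keeps that protection only if the mediator equation contains no covariate that treatment can change.

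A 3-month count of moderate-or-greater pain prompts is close to an interim version of the pain outcome, which the article hypothesises will fall under INTV. Entry also requires pain of 4 or more on the rating scale, so success should mean fewer such prompts. Conditioning on the count can remove part of the effect on the mediator. It can also induce an association between arm and unmeasured severity.

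The same prompts define the mediator, so a participant with none has no score. If INTV works, that may be more common in INTV.

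At stake is the explanation of how INTV works, which is a named secondary aim and a stated reason for using EMA.

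**Working it through.** **The plan's own figures.** The article says "A sample size of 250 (*n* = 125 to each condition) will be randomized". With 20% attrition, 125 × 0.8 = 100 per arm are analysed. For d = 0.40 and two-sided 0.05, power is Φ(0.40/√(2/100) − 1.960) = Φ(0.868) = 0.807, so the stated 80% reproduces. The mediation power claim (above 80% for small-to-medium paths) is also plausible: a simulated joint-significance test at N = 200 gives 0.65, 0.79 and 0.92 for a = b = 0.20, 0.23 and 0.26. Neither figure settles the present point.

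**When path a is distorted.** Let X be arm, M the mediator, E the 3-month relevant-event count and Y the outcome. In a linear model with E added to the mediator equation,

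a′ = a − c·τ,

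where τ is the total effect of X on E and c is the slope of M on E given X. Path a is distorted only if both are non-zero: treatment changes the count, and the count is related to the mediator within arm.

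**Size under assumed structures.** The documents give no path values or event rates. I assume X→M = 0.4 (except in D), M→Y = −0.3, unit residual SDs, and a direct X→E effect of −g with g from 0 to 0.4.

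- *A. The mediator lowers the count* (M→E = −0.3; E→Y = h, from 0 to 0.5). Here τ = −(0.12 + g) and c = −0.3/1.09, so a′ = (0.4 − 0.3g)/1.09: 0.367 at g = 0 and 0.257 at g = 0.4. The true indirect effect is 0.4 × (−0.3 − 0.3h). With E in both equations, the estimate is 0.3 × 0.367/0.12 = 92% of truth (g = h = 0), down to 0.3 × 0.257/0.18 = 43% (g = 0.4, h = 0.5). Without E it is 100%.
- *B. Unmeasured severity drives the count, mediator and outcome* (strength u = 0.5). a′ = 0.4 − g·u²/(1 + u²) = 0.32 at g = 0.4. Path b is −0.3 − u²/(1 + 2u²) = −0.467 with E, and −0.3 − u²/(1 + u²) = −0.50 without. Against a true value of −0.12, the product is 0.32 × 0.467/0.12 = 124% with E and 0.4 × 0.50/0.12 = 167% without. At g = 0 it is 0.4 × 0.467/0.12 = 156% with E.
- *C. The count lies between arm and mediator* (E→M = −0.3, E→Y = 0.3). With E in both equations: 0.12/0.138 = 87% at g = 0.2 and 0.12/0.156 = 77% at g = 0.4. With E in the outcome equation only: 100%. With E left out, path b becomes −0.3 − 0.09/1.09 = −0.383, giving 0.383/0.3 = 128%.
- *D. As B, but no true effect on the mediator.* a′ = −0.2g, so a spurious indirect effect of 0.04 × 0.467 = 0.02 to 0.08 × 0.467 = 0.04 appears. Without E it is zero.

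**With actual counts.** Simulated with a true path a of 0.40 and a mean of about 6 events, adjusted path a depends heavily on the count distribution:

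- 0.16 for Poisson counts, with arm and mediator each lowering the log rate by 0.2.
- 0.33 for the same effects with between-person overdispersion (gamma shape 2).
- 0.37 for shape 1 with effects of −0.3 (arm) and −0.1 (mediator).
- 0.40, unchanged, when arm lowers the log rate by 0.35 but the count is unrelated to the mediator within arm.

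**Participants without a score.** For negative binomial counts, P(no event) = (k/(k + μ))^k.

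- k = 1, control mean 10, rate ratio 0.6: 1/11 = 9.1% of CTL and 1/7 = 14.3% of INTV.
- k = 1, control mean 5, rate ratio 0.6: 1/6 = 16.7% and 1/4 = 25.0%.
- k = 2, control mean 25, rate ratio 0.8: (2/27)² = 0.5% and (2/22)² = 0.8%.

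The EMA schedule allows up to 5 × 15 = 75 prompts.

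**The case against.** The article never says the count is the 3-month one. The covariate sentence also covers the moderation models, which use pre-randomisation EMA, and there the count is harmless. That stands, and so does the gap over which equation the count enters. However, a count of the events that form a 3-month score most naturally comes from the same period, and nothing exempts mediation. If baseline counts are meant, the text should say so.

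A reader might infer more: that the mediated effect is certainly biased towards zero, that the randomised comparison is destroyed, and that INTV's successes drop out of the analysis. The documents do not support this:

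- Bias in path a also needs a link between count and mediator. Under a shared cause, adjustment brings the product closer to the truth (structure B). Entered only in the outcome equation, the count can be harmless or helpful (structure C).
- Reducing drinking opportunities is nowhere stated as a target. Opportunity is described as a setting in which self-regulation should improve.
- For people selected for chronic pain and prompted up to 75 times, having no qualifying pain event may be rare.
- Restricting scores to exposed prompts defines the context-specific hypothesis and is not itself an error. A mean over all prompts would change that hypothesis. It may not be obtainable either, since the EMA section does not list self-regulation among the random-prompt items.
- The analysis text refers to questionnaire data in parallel, and Table 1 has the goal-systems questionnaires at month 3. A mediation route that needs no event count therefore appears available.

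Handling of missing scores may properly sit in an analysis plan that is not shown. The covariate is different, because the article states it.

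**Conclusion.** The point holds in a limited form. On the natural reading, the EMA mediation models condition on a post-randomisation count that, for pain, follows from what INTV is meant to change. If that count is in the mediator equation and related to the mediator, path a is no longer a randomised contrast and the indirect effect can be biased.

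Neither size nor direction can be fixed from the documents. With the count in both equations, the illustrative range is 43% to 156% of truth. The upper end reflects confounding of path b, which is larger still without the count, so it is not damage done by adjustment. Every magnitude rests on assumed paths and event rates. Unequal loss of mediator scores is possible, from negligible to several percentage points between arms.

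Only the EMA mediation analyses are affected. This is a secondary aim, and the point ranks below must-fix.

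**What to change.** In the EMA mediation models, replace the 3-month relevant-event count with the baseline-EMA count, and add the baseline mediator and baseline outcome. Keep the context-specific score as the main mediator. Report 3-month counts by arm, or model them as a parallel mediator. Give the estimate adjusted for the 3-month count only as a sensitivity analysis, naming the equation it enters. Keep participants with no qualifying event in the structural equation model by full-information likelihood. The event count can stay in the baseline-EMA moderation models.

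The cost is a change of wording and one extra model. The main model would no longer adjust directly for how many events each 3-month score rests on. The change restores the randomised contrast behind path a. Path b would still depend on the absence of unmeasured confounding, and the likelihood approach on scores being missing at random given the modelled variables.
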